# Mesenteric excision and Kono‐S anastomosis trial (MEErKAT): A study protocol for a multicentre, 2 × 2 factorial, randomised controlled, open‐label superiority trial

**DOI:** 10.1111/codi.70212

**Published:** 2025-09-08

**Keywords:** Crohn's disease, inflammatory bowel disease, surgery

## Abstract

**Aim:**

Controversy exists over whether surgical technique can reduce recurrence following Crohn's resection. This study compares the rate of endoscopic recurrence after different approaches to mesenteric excision (extended/close) and anastomosis (Kono‐S/standard of care) in adult patients undergoing ileocolic resection for primary or recurrent Crohn's disease.

**Method:**

MEErKAT is a UK multicentre, 2 × 2 factorial, randomised, controlled, open‐label superiority trial where participants (target sample size = 308) are blinded and centrally randomised (1:1:1:1) to one of four groups: (1) Kono‐S + extended mesenteric resection. (2) Kono‐S + close mesenteric resection. (3) Standard anastomosis + extended mesenteric resection. (4) Standard anastomosis + close mesenteric resection. The primary outcome is time to endoscopic recurrence of disease (up to 3 years follow‐up). Secondary outcomes include rates of severe and symptomatic recurrence, complications, and quality of life scores. The locality of recurrence will be investigated using endoscopic assessment of the mucosa relative to mucosal tattoos placed at the time of operation. The degree and anastomotic locality of different immune cells will be compared before and after each intervention to better understand the mechanistic processes driving disease recurrence.

**Conclusion:**

This study will robustly evaluate the efficacy of the Kono‐S anastomosis technique and extended mesenteric excision in reducing endoscopic recurrence rates. The additive effect of these techniques and local tissue immune response will be investigated. This will provide important evidence to guide the optimal surgical technique and improve our understanding of the processes leading to recurrent disease.

What does this paper add to the literature?The proposed study will evaluate the efficacy of the Kono‐S anastomosis and extended mesenteric excision in reducing endoscopic recurrence rates for patients undergoing ileocolic resection for primary or recurrent Crohn's disease.

## INTRODUCTION

Crohn's disease (CD) is a relatively common chronically relapsing inflammatory condition of the gastrointestinal tract [1]. Despite advances in medical therapy, a large proportion of patients eventually require resection of diseased bowel, with over one third of these people requiring further surgery within 10 years [2].

Animal models and pathological specimens indicate that patterns of recurrence begin at the mesenteric border of the anastomosis [3, 4, 5]. The mechanisms believed to drive recurrence involve faecal stasis and alterations in the gut microbiome [6]. Some highlight the significance of mesenteric vascular anatomy, emphasising that the mesenteric border of the bowel relies on end arteries, while the antimesenteric border has collateral supply. Therefore, disease in the mesentery is likely to disrupt the blood supply to the mesenteric border before the antimesenteric border, resulting in the observed pattern of ischaemic ulceration [7, 8]. Supporting this theory, studies on strictureplasty show a very low site‐specific surgical recurrence rate, despite leaving diseased bowel and mesentery in place [9].

Alternative theories propose the mesentery as the disease focus, observing elevated visceral fat content, increased lymphatic vascular density at the resection margin, and the presence of granulomata in the mesenteric lymph nodes, all associated with recurrence [10, 11, 12]. This leads to the concept that extended resection is required to eliminate the disease focus.

These theories have prompted surgeons to consider whether the techniques of resection and anastomosis can influence recurrence rates. Different anastomotic configurations and techniques have been tested, yielding inconsistent results [13, 14]. Present consensus supports a wide lumen configuration, achieved through a stapled side‐to‐side technique [15, 16].

Two techniques, despite limited evidence, have gained attention due to a seemingly spectacular reduction in recurrence [17]. The Kono‐S anastomosis has a wide‐lumen, antimesenteric configuration to address the predisposition for mesenteric border recurrence. A systematic review showed several low‐quality studies and one high‐quality randomised controlled trial (RCT) affirming the safety of this technique [17]. The findings also suggested a remarkable 65% reduction in endoscopic recurrence after 6 months (22.2% in the Kono‐S group compared to 62.8%). If this level of reduction in recurrence rates holds true, the Kono‐S technique will have profound implications for disease management. However, there is a need for high‐quality data to better determine the effectiveness of this technique, with some comparative studies ongoing (e.g. NCT 03256240).

An alternative concept proposes the mesentery as the primary driver of disease, advocating for extended resection of the diseased mesentery, with the anastomosis being considered irrelevant to recurrence [18, 19]. The recent evidence supporting extended resection of the mesentery is limited and contradictory. The SPICY randomised controlled trial comparing extended mesenteric resection with conventional mesenteric resection did not show a difference in endoscopic recurrence rates 6 months after surgery (42% in the extended mesenteric group compared to 43% in the mesenteric sparing resection group) [20]. In contrast, the interim results of the MESOCOLIC trial favour a more radical resection in reducing endoscopic recurrence [21]. The authors speculate that the different methods of extended mesenteric excision (high ligation vs. preservation of the ileocolic vessels) are responsible for the observed difference.

There are commonalities with the techniques of Kono‐S anastomosis and extended mesenteric resection that may explain their potential effectiveness. Both isolate the anastomosis from the diseased mesentery. Kono‐S achieves this through a totally antimesenteric anastomosis placed as far away as possible from the mesentery, while extended mesenteric resection removes the theoretical disease driver. A combined approach is technically feasible and may improve efficacy. If either or both interventions result in reduced recurrence, understanding the underlying mechanism of action becomes a crucial question. To explore this, we will examine the locality of any mucosal recurrence. The prevailing notion is that CD arises from the interplay of genetically inheritable traits and environmental factors, including the microbiota, leading to innate and adaptive immune cell‐mediated inflammation [22]. Analysing the immune cell phenotypes in the mucosa of the different combinations of resection and anastomosis will provide insights into the impact each intervention has on the mechanism of inflammation [23, 24, 25]. Examining visceral fat area, anastomotic locality of immune cell populations, with a specific focus on T cell activation and exhaustion, will enable us to explore potential underlying mechanisms of action.

We propose a protocol for a UK multicentre, superiority, 2 × 2 factorial, randomised, open‐label trial with a 1‐year follow‐up (−6 months/+3 months). Participants will be randomised (1:1:1:1) to one of four groups:
Kono‐S + extended mesenteric resection;Kono‐S + close mesenteric resection;Standard anastomosis + extended mesenteric resection;Standard anastomosis + close mesenteric resection.

Our trial will investigate relevant clinical and mechanistic outcomes on: (1) the Kono‐S anastomosis; (2) extended mesenteric excision; (3) the locality of recurrence after surgery; and (4) local tissue immune response and its association with surgical recurrence.

The main aim of the study is to compare recurrence after standard mesenteric excision or extended excision and standard anastomosis or Kono‐S anastomosis (with or without extended mesenteric excision).

## METHODS

This protocol has been written according to SPIRIT guidelines.

### Study setting

The study will recruit patients aged over 18 years undergoing ileocolic resection for primary/recurrent CD where an anastomosis is carried out. The study will be run nationally within the United Kingdom across up to 27 centres, recruiting an average of one participant per 4 months over a maximum of 45 months.

### Eligibility criteria

#### Inclusion criteria

Patients aged 18 years and over.Patients undergoing ileocaecal resection for primary/recurrent CD where an anastomosis is carried out.

#### Exclusion criteria

Patients with markedly extensive inflammation affecting the vascular root of the mesentery seen on imaging or at operationPatients undergoing stoma formation proximal to the anastomosisPatients who have a contraindication to subsequent colonoscopyPatients unable to give full informed consentPatients who are pregnantPatients who, in the opinion of the principal investigator, do not meet the criteria for relevant surgery

In a very small subset of patients, it may be the case that extensive mesenteric inflammation is only seen intraoperatively, meaning the patient is ineligible for the trial. Participants should therefore not undergo randomisation until the diseased area can be visually assessed intra‐operatively.

### Interventions

There are two groups of mesenteric excisions and two groups of anastomoses.

### Mesenteric excision

#### Extended mesenteric excision

The mesentery is resected up to the origin of the ileocolic trunk but preserving the ileocolic vessels as described, in detail, in the SPICY trial [20, 26]. In participants who have markedly extensive inflammation affecting the vascular root of the mesentery seen on imaging or at operation, these should not undergo extended resection due to the risk of vascular injury and should be excluded from the trial.

#### Close mesenteric excision

The mesentery is resected within 3 cm of the border of the bowel, leaving most of the mesentery in situ.

### Anastomosis

#### Kono‐S

The resected bowel is stapled perpendicular to the mesentery and the stapled ends sutured together to form the supporting column. Seven centimetre antimesenteric enterotomies are made from 1 to 1.5 cm from the stapled resection margin and a side‐to‐side anastomosis created by suturing the enterotomies together.

#### Standard of care

Standard care is essentially surgeons' preference of anastomosis. Anastomosis may utilise staples or sutures and has a configuration of either end to end, functional end to end, or end to side.

The mode of access (open/laparoscopic/robotic), closure technique and post‐operative care are according to usual practice for that participating centre.

For all groups the mesenteric incision will be made proximal to the mesenteric transition zone [27], while the distal incision will be placed where both the mesentery and intestine are macroscopically normal immediately distal to the region of disease. Each technique consists of components familiar to bowel surgeons.

Every participating surgeon will have been mentored for the Kono‐S anastomosis and will have carried out at least 2 procedures outside the trial. A video of each technique will be created and distributed to all surgeons. We will run dedicated training sessions for all surgeons involved in the trial. Two independent reviewers will review images of the resection specimen to ensure adequate quality and extent of mesenteric excision.

Post‐operative follow‐up and colonoscopic assessment at 6–12 months are part of standard practice [28]. Localisation of recurrence will be aided by a tattoo of the mesenteric border of the anastomosis at the time of surgery using carbon black.

### Outcomes

#### Primary outcome

Time to endoscopic recurrence of disease (up to 3 years follow‐up) from the date of randomisation using the Modified Rutgeerts score (≥i2) [29]. With a subgroup analysis of i2a and i2b groups.

Endoscopic recurrence is an early surrogate for surgical recurrence and is frequently used as a primary outcome in related previous trials [21, 30] and ongoing trials. For quality assurance, the endoscopist will be blinded, and the Modified Rutgeerts score will be checked by two independent and blinded assessors.

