**FIGURE 1 codi70212-fig-0001:**
[figure not shown]
Study flowchart demonstrating participant journey through the trial from identification, enrolment, treatment allocation and follow‐up.

**TABLE 1 codi70212-tbl-0001:** Schedule of assessments during the study.

	Baseline	Operation	6 weeks	12 months (−6 to +3 months)	Study end (up to 5 years)
Eligibility assessment	X	X			
Consent	X				
Medical history	X				
Concomitant medications	X		X	X	X
Demographics	X				
IBD‐Control	X		X	X	
CDAI	X		X	X	
EQ‐5D	X		X	X	
Randomisation		X			
Mesenteric disease activity index		X			
Adverse events		X	X	X	
Colonoscopy				X	X (via note review)
Blood samples	X			X	
Mucosal/mesenteric biopsies		X		X	
Surgical recurrence				X	X (via note review)

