### Sample size

The primary outcome will be the time to endoscopic recurrence (ER) post‐randomisation (Modified Rutgeerts score ≥ i2). All participants will be followed up for a minimum of 6 months post‐randomisation and up to a maximum of 3 years. The best existing data indicates ER rates of approximately 65% on conventional surgery and 24% on Kono‐S surgery at 12 months [34]. Other published data on the rate of endoscopic recurrence after conventional surgery varies from 58% to 93% [28, 35, 36, 37]. The systematic review unfortunately found no published data on the ER rates after close or extended mesenteric resection [16]. In a survey of 34 surgeons, 71% were persuaded to change practice based on a reduction in endoscopic recurrence to 30% or less after 12 months.

The sample size calculation for the 2 × 2 factorial design assumes: 90% power; 5% (two‐sided) significance level; and estimated reduction in 1‐year endoscopic recurrence rates from 52.5% to 32.5%. Using the Freedman method a total of 112 recurrences are required [38]. After accounting for surgeon effects (assuming each of 12 sites would have 2 surgeons, an ICC of 0.01 and 15 patients per surgeon) and an attrition rate of 3%, the target sample size is 154 per group for each comparison.

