### Data collection

Baseline data will be collected by a research nurse or clinician using specific case report forms (Table 1). Participants will be given a diary to complete 7 days prior to the day of surgery to enable the Crohn's Disease Activity Index (CDAI) to be calculated (Appendix 2). Operative details will be recorded by the operating surgeon. Six‐week and 6‐ to 12‐month follow‐up data will be collected by a research team member who is blind to allocation. Standard colonoscopic follow‐up will be collected by a colonoscopist not involved in the trial. Colonoscopists will collect mucosal biopsies and recurrence data, relative to the small bowel mesenteric tattoo. At the end of the study (12–57 months after surgery) further data will be collected by a team member who is blind to allocation.

Participants may withdraw their consent for the study at any time. Although the participant is not required to give a reason for discontinuing their study treatment, a reasonable effort will be made to establish this reason while fully respecting the participants’ rights.

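### The primary endpoint runs to 3 years with one scheduled colonoscopy, so later recurrences depend on routine re-scoping; the right-censored Weibull model handles this badly, and the follow-up statements conflict

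*Protocol article*

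**What the plan says.** Under Primary outcome, the protocol article sets "Time to endoscopic recurrence of disease (up to 3 years" of follow-up), counted from randomisation, with recurrence defined as a Modified Rutgeerts score of i2 or above. Sample size and Statistical methods repeat the 3-year horizon.

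Table 1 shows colonoscopy at one study visit, 12 months (−6 to +3 months). Its only other colonoscopy entry is at study end, obtained by note review. Interventions and Discussion also describe one assessment, at 6–12 months.

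Statistical methods specifies a mixed-effects Weibull model, with patients free of reported recurrence censored at the last date they were known to be free of it. It describes no interval censoring.

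Follow-up length is given in several ways:
- Introduction: "open‐label trial with a 1‐year follow‐up (−6 months/+3 months").
- Sample size: "followed up for a minimum of 6 months post‐randomisation and up to a maximum of 3 years".
- Data collection: "At the end of the study (12–57 months after surgery").
- Table 1: "Study end (up to 5 years").

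**The concern.** Endoscopic recurrence is seen only when someone looks. Up to about 15 months every participant is due to be looked at once. From then to 3 years, a recurrence can count only if routine care happened to include a colonoscopy. The article does not say why or how often such colonoscopies occur, but symptoms are one plausible prompt, and the operating team knows the allocation.

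The true onset lies somewhere between two colonoscopies. If recurrence is dated at the colonoscopy that found it, and everyone else is censored at the last clear colonoscopy, both event times and censoring times depend on when and whether people were scoped. What is at stake is the size of both factor effects, the power, and, if re-scoping differs by arm, the false-positive rate.

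The inconsistent follow-up statements add to this, because they leave open which recurrences belong to the primary endpoint.

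**Working it through.** **1. The plan's own figures (Sample size).** Inputs: 1-year recurrence 52.5% against 32.5%, 90% power, 5% two-sided, ICC 0.01, 15 patients per surgeon, 3% attrition.

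- HR = ln(1 − 0.325) / ln(1 − 0.525) = 0.528.
- Freedman events = (1.960 + 1.282)² × [(1 + 0.528)/(1 − 0.528)]² = 110.1, so 111 (stated: 112).
- Design effect = 1 + 14 × 0.01 = 1.14. Mean 1-year rate = (0.525 + 0.325)/2 = 0.425.
- N = 112 / 0.425 × 1.14 / 0.97 = 309.7, or 304.5 from the unrounded 110.1 (stated: 308).

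The stated figures reproduce.

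**2. Are recurrences after 1 year needed?** Expected recurrences at 12 months = 308 × 0.97 × 0.425 = 127. Dividing by 1.14 gives 111, against 112 required. A simple comparison of 52.5% with 32.5% needs 127 per level, and 127 × 1.14 / 0.97 ≈ 150, within the planned 154. The calculation relies on nothing beyond 1 year.

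**3. Illustration by simulation.** These assumptions are not in the article: exponential onset; scheduled colonoscopy uniform over 6–15 months; 149 per level (308 × 0.97 / 2); no clustering; recurrence dated at detection. Among those clear at the scheduled colonoscopy, 60% of later recurrers and 15% of the others are re-scoped at 18–36 months. The ranges cover repeated runs of 300 to 800 simulated trials.

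| Data and model | Estimated HR (true 0.53) | Power |
|---|---|---|
| All colonoscopies, right-censored (as planned) | 0.67–0.69 | 63–72% |
| Scheduled colonoscopy only, right-censored | about 0.61 | 70–74% |
| Scheduled colonoscopy only, interval-censored | 0.52–0.53 | 88–93% |
| All colonoscopies, interval-censored | 0.55–0.56 | 94–96% |

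Most of the power loss is already present with the scheduled colonoscopy alone, so it comes from the right-censored treatment of the data. Late colonoscopies attenuate the hazard ratio further.

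**4. False positives with no true effect.**
- Recurrers re-scoped at 60% in one arm and 40% in the other: 11–17% under the planned model; 4–6% with interval censoring on all colonoscopies; about 4% with the scheduled colonoscopy only.
- All recurrence-free patients re-scoped at 60% against 30%, at 15–36 months: HR 1.28 or 0.79 depending on which arm is scoped more, with rejection in 36–39%.
- Equal re-scoping in both arms: about 6% when symptom-driven as in step 3, and 8–10% when 60% or 30% are re-scoped at random. The large inflation therefore needs a difference by arm.

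**5. Follow-up statements side by side.**
- 1 year (Introduction) against a 3-year maximum (Primary outcome, Sample size, Statistical methods).
- A 6-month minimum (Sample size) against study end no earlier than 12 months (Data collection).
- A 6–15 month window (Introduction, Table 1) against 6–12 months (Interventions, Data collection, Discussion).
- Study end at up to 57 months or 5 years, with no rule for recurrences found after 3 years.
- Two endoscopic secondary outcomes are set at 3 years, although Table 1 has no 3-year visit.

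**The case against.** The strongest reply is that a survival model can use irregular observation, and that the trial protects its endpoint. Much of this stands.

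- **Model.** A reader might infer that late routine colonoscopies bias the comparison whatever model is used. The calculations do not support that. Interval censoring on all colonoscopies gave an HR of 0.55–0.56, the highest power, and near-nominal false positives in the same scenarios.
- **Blinding.** A reader might infer that the blinded endoscopist and the two blinded assessors apply only to the 12-month endoscopy. The Primary outcome section states both without a time limit; only the Blinding section mentions 12 months. Participants are blinded, and Data collection has end-of-study data gathered by someone blind to allocation. This lowers the risk. It does not blind the decision to re-scope, and the article does not show how images from routine colonoscopies would reach the central assessors. The full protocol may cover that last point.
- **Follow-up lengths.** They are not all in conflict. The figure of 57 months equals 45 months of recruitment plus 12 and fits within 5 years. The 6-month minimum matches the lower end of the visit window. The conflicts that remain are those listed in step 5 of the working.
- **Assumed rates.** The re-scoping rates are invented, and nothing in the article says how often late colonoscopies happen. The simulations show sensitivity and are not forecasts.

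**Conclusion.** The concern holds in a limited form. A 3-year time-to-event endpoint resting on one scheduled colonoscopy leaves ascertainment after about 15 months to routine care, and the right-censored Weibull model as described does not handle that. Under the assumed rates, the hazard ratio is estimated at about 0.67 instead of 0.53, with power near 71% instead of 90%. False positives reach about 11–17% if recurrers are re-scoped at 60% against 40% by arm, and more if the difference in re-scoping is wider. These sizes depend on the assumed re-scoping rates, exponential onset, and dating recurrence at detection, which the article does not state but which is the natural reading of an ordinary right-censored model.

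A reader might also conclude that the sample size is wrong because it uses 1-year rates. It is not: it reproduces, and a hazard ratio may be set from 1-year rates. What it shows is that the design does not need the late events. The conflicting follow-up statements are errors of wording, but they decide which events count.

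**What to change.** 1. Make the primary analysis endoscopic recurrence at the colonoscopy scheduled in Table 1 (6–15 months), which matches the 1-year rates behind the sample size.
2. Analyse it with an interval-censored Weibull model, keeping the planned factors and random effects. This part is essential: restricting the endpoint under the right-censored model leaves power at about 70–74%, against 88–93% with interval censoring. Allowing for clustering (149 / 1.14 ≈ 131 effective per level), power is about 87–91%.
3. Report note-review colonoscopies up to 3 years as a supportive interval-censored analysis. If the 3-year primary endpoint is kept, interval censoring is the minimum change.
4. Reconcile the follow-up length and visit window across Introduction, Interventions, Primary outcome, Secondary outcomes, Sample size, Data collection, Discussion and Table 1. Include the endoscopic secondary outcomes set at 3 years, and add a rule for recurrences found after 3 years.

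The cost is an amendment to wording and model, with no new visits. The downside is that late note-review events leave the primary analysis. In the illustration, keeping them with interval censoring had slightly higher power (94–96%), so dropping them gives up a little power in return for an endpoint observed on the same schedule in both arms.
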